### Outcome evaluation

#### Baseline characteristics

Patients’ demographic characteristics including age, gender, ethnicity, marital status, cohabitation status, educational attainment, occupation, predisposing factors, prior therapies, history of illness, medication history, vital signs and weight for height will be considered. Baseline data for the enrolled participants will be recorded before randomization.

#### Primary outcomes

Cognitive status will be evaluated with the MoCA and MES. The primary efficacy endpoints are the improvement rate for MoCA scores and MES scores, which will be measured before and after treatment in both groups. The MoCA has high sensitivity and specificity in distinguishing normal elderly individuals from those with MCI and mild Alzheimer's disease and can detect slight cognitive impairment [16]. The MES has been confirmed to be a valid and easily administered screening tool for MCI, and the score is independent of education and can also be used to evaluate individuals [17].

$$\text{Improvement rate} = \left[\left(\text{posttreatment score}-\text{pretreatment score}\right)/\text{pretreatment score}\right]\times100\%.$$

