**Methods:**

This study is a multicentre, randomized, double-blind, parallel-group, controlled trial. Based on the results of previous clinical trials, 280 elderly patients with MCI will be randomly divided into a treatment group (*n* = 140) and control group (*n* = 140). The study will last 33 weeks, including 1 week of screening, 8 weeks of intervention, and 24 weeks of follow-up. The primary outcomes will be the changes in Montreal Cognitive Assessment (MoCA) and Memory and Executive Screening (MES) scores before and after the intervention. The secondary outcome measures will be homocysteine (HCY) levels, Functional Assessment Questionnaire (FAQ) scores and event-related potential (ERP) detection in typical cases. The TCM symptom scale is a combined measure of syndrome differentiation and treatment. During this study, the classifications and characteristics of adverse events, the times of occurrence and disappearance, the measures of treatment, their impact on the primary disease, and outcomes will be reported truthfully.

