## Methods

### Study design

This study is a multicentre, randomized, double-blind, parallel-group, controlled trial. The objective of this trial is to evaluate the clinical efficacy and safety of YSF granules in elderly patients with MCI. The trial protocol (version 2.0, April 27, 2020) has been registered with the Chinese clinical trial registry (No. ChiCTR2000036807). The period for research recruitment is from August 5, 2021, to December 31, 2023. We present the following article in accordance with the SPIRIT 2013 reporting checklist. For more details about the checklist, please see Additional file 1.

Before the beginning of the clinical study, all researchers will be trained on the standardized process and scale evaluation consistency to ensure the clinical trial quality and data credibility of each centre. A total of 280 elderly patients with MCI will be randomly divided into a treatment group and a control group in a 1:1 allocation ratio. It will be carried out in three clinical centres in Shanghai, 140 subjects will be recruited at Shanghai Municipal Hospital of TCM, and we plan to recruit 70 subjects from Shanghai Qingpu District Hospital of TCM and 70 subjects from Shanghai Jiading District Nanxiang Hospital. All participants will experience a 1-week screening period, with an 8-week treatment period and follow-up visits at 24 and 48 weeks. The primary efficacy outcome measures will be the change in the Montreal Cognitive Assessment (MoCA) and Memory and Executive Screening (MES) scores, which will be used to assess cognitive function following the interventions. The TCM symptom scale is a combined measure of syndrome differentiation and treatment. Safety outcome markers will include hepatic and renal functions, electrocardiogram data, routine blood and urine test results, and severe clinical discomfort. The schedule of enrolment, interventions, assessments and data collection is presented in Table 1. The study will follow the Helsinki Declaration and the Good Clinical Practice guidelines. Ethical approval was granted by the Ethics Committee of Shanghai Municipal Hospital of TCM (approval no. 2020SHL-KY-06). Each subject could only be included in this study once and signed an informed consent form prior to study participation. The results of the study will help provide a clinical basis and TCM treatment plan for standardized diagnosis and treatment of MCI. The flowchart of this study is illustrated in Fig. 1.

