### Statistical plan

#### Sample size calculation

The necessary sample sizes were calculated for the two primary outcomes, namely, the MoCA and MES. With reference to our previous study [21], the following parameters were used: the mean MoCA score (*μ*_r_) in the treatment group was 25.67; the mean MoCA score (*μ*_c_) in the control group was 23.36; we assumed that the superiority margin (Δ) was 1.20; the standard deviation (σ) was 2.21; the type I error rate (α) was set to the usual level, a unilateral value of 0.025), with Z_α/2_ = 1.96, the type II error rate (β) was set to a unilateral value of 0.05, with Z_β_ = 1.645; the ratio (K) of the treatment group size (*n*_1_) to the control group size (*n*_2_) was K = 1 (*n*_1_ = *n*_2_ = 104). Considering that there are three research centres in this study and a 20% dropout rate, the logistic regression analysis suggested that the sample size should be 15 to 30 times the number of indices being analysed plus an extra 30 patients, for a total required sample size of 280 patients (140 patients per group).

For the second primary outcome, we set the mean MES scores to 82.83 in the treatment group and 73.50 in the control group, with an SD of 7.83 [22]. We assumed that the superiority margin was 3.92 (1/2 standard deviation); we calculated that we would need a total of 122 patients (66 per group) to allow for a 20% dropout rate. Of the necessary sample sizes estimated for the two primary outcomes, the larger value was selected as the sample size for this study. The formula for calculating the sample size is as follows:

$$\begin{array}{c}{\mathrm n}_{\mathrm c}=\frac{\left({\mathrm Z}_{\displaystyle\mathrm\alpha/2}\;+\;{\mathrm Z}_{\mathrm\beta}\right)^2\;\mathrm\sigma^2\;\left(1+{\displaystyle\frac1{\mathrm k}}\right)}{\left(\mu_r-\mu_c-\mathit\triangle\right)^2}\\{\mathrm n}_{\mathrm r}={\mathrm{Kn}}_{\mathrm c}\end{array}$$

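### The primary endpoint is defined as a percentage improvement rate, but the sample size and superiority margins are set in score points, so the stated power and margins do not apply to it

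*Protocol article*

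**What the plan says.** Four places in the protocol article bear on the primary variable.

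- **Outcome evaluation, Primary outcomes:** "The primary efficacy endpoints are the improvement rate for MoCA scores and MES scores". The displayed formula is (post − pre)/pre × 100%.
- **Abstract, Methods:** "The primary outcomes will be the changes in Montreal Cognitive Assessment (MoCA) and Memory and Executive Screening (MES) scores before and after the intervention".
- **Study design:** "The primary efficacy outcome measures will be the change in the Montreal Cognitive Assessment (MoCA) and Memory and Executive Screening (MES) scores".
- **Sample size calculation:** the MoCA mean "in the treatment group was 25.67" and "in the control group was 23.36"; "we assumed that the superiority margin (Δ) was 1.20"; "the standard deviation (σ) was 2.21". For MES the means are 82.83 and 73.50, the SD 7.83 and the margin 3.92. One-sided α is 0.025 (z = 1.96) and β is 0.05 (z = 1.645), so the planned power is 95%.

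The Statistical analyses section sets a threshold of 0.033 for the two primary outcomes but does not say which of these variables is tested.

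**The concern.** A percentage of baseline and a difference in points are different variables. They have different units and different SDs, and the same data can give different p-values. The only definition with a formula is the percentage, yet every planning figure is a score in points. A reader of the final report could not check the planned superiority margin against the endpoint as defined. If one section is followed for the analysis and another for the power statement, the two describe different hypotheses. Choosing between percentage and points after the data are seen would also leave room for a selective primary result on each of two scales.

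**Working it through.** **1. Reproduce the plan's own figures.** The printed formula is n per group = (Zα/2 + Zβ)² σ² (1 + 1/K) / (μr − μc − Δ)², with K = 1 and (1.96 + 1.645)² = 3.605² = 12.996. All inputs are from Sample size calculation.

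- MoCA: 25.67 − 23.36 − 1.20 = 1.11. n = 12.996 × 2.21² × 2 / 1.11² = 103.03, rounded up to 104. This is the stated figure.
- MES: 82.83 − 73.50 − 3.92 = 5.41. n = 12.996 × 7.83² × 2 / 5.41² = 54.45, rounded up to 55. Then 55 × 1.2 = 66, the stated figure per group.

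Both reproduce from score levels, SDs and margins in points. The powered quantity is a score, not the improvement rate.

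**2. Try to express the margin on the percentage scale.** Margin in percent = 100 × margin / baseline score.

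| Baseline score | MoCA margin, 1.20 points | MoCA planned difference, 2.31 points |
|---|---|---|
| 20 | 6.0% | 11.55% |
| 25 | 4.8% | 9.24% |

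For MES, 3.92 points is 5.6% at a baseline of 70 and 4.9% at 80. The baselines are illustrative, since the document gives no baseline mean. No single percentage corresponds to either margin.

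**3. Can power for the percentage be recovered?** That needs the baseline mean, the baseline SD and the correlation between pre and post scores. The document gives none of them. Assume:

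- MoCA baseline mean 20 to 23, baseline SD 2.21 to 3, values at or above 25.5 removed;
- post-treatment SD 2.21 and correlation 0.3 to 0.9;
- a constant 2.31-point effect and two-sided α 0.05;
- the margin converted patient by patient.

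The average margin then becomes about 5.4 to 6.2 percentage points. The number per group for 95% power runs from about 23 to 299, against the stated 104. With 140 × 0.8 = 112 completers per group, power runs from about 60% to over 99%. The range lies on both sides of the plan, so the direction is not determined.

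**4. Change in points against final score.** Under randomization both have the same expected between-arm difference, so the 1.20 and 3.92 margins fit either. Only the SD differs. With equal pre and post SDs of 2.21, the SD of change is 2.21 × √(2(1 − r)), and the MoCA n per group is 145, 104, 62 and 21 at assumed r = 0.3, 0.5, 0.7 and 0.9. The two coincide at r = 0.5. The units conflict is therefore percentage against points.

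**5. Baseline-adjusted score.** The residual variance is 2.21² × (1 − r²), so the MoCA requirement is 103.03 × (1 − r²): 77.3 (78 per group) at r = 0.5 and 52.5 (53 per group) at r = 0.7. At r = 0 it is the plan's 104.

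**The case against.** The section headed Primary outcomes is the natural place for the definition and the only one with a formula. The words for change in the abstract and Study design never say points, so they could be shorthand for the pre-to-post comparison that the formula quantifies. The sample size section gives planning means, not an endpoint definition. This stands as far as it goes: the abstract and Study design may be reconcilable with the percentage. It does not reconcile the percentage with the sample size section, whose margins are in points and have no counterpart on the other scale. A separate analysis plan could choose one version, but it would still contradict the rest of this article.

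Two stronger readings are tempting and not supported.

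- **That there are three incompatible scales.** Change and final score share the point scale and the same expected treatment difference.
- **That the percentage loses power.** An unadjusted percentage test does look weak beside a baseline-adjusted score, but most of that gap comes from the adjustment. An illustrative simulation assumed 112 per arm, baseline mean 22 and SD 2.2 below 26, a true difference of 0.6 points and α 0.033. With equal adjustment, power was 58% for the percentage and 59% for the score at correlation 0.5, and 76% for both at 0.7. The 0.6-point effect is not in the document, which plans on 2.31. In the same setting the percentage was only mildly skewed and correlated about 0.99 with the point change.

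**Conclusion.** The concern holds as a conflict of definition. The primary endpoints are defined as a percentage, while the trial is sized, and its superiority margins are set, on scores in points. The 104 and 66 per group reproduce on the point scale, and the document has no mean, SD or margin for the percentage. The 95% power and the margins of 1.20 and 3.92 therefore do not apply to the endpoint as written. This conclusion rests only on figures in the document.

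It should not be read as a finding that the trial is underpowered. Whether the percentage endpoint has more or less power depends on inputs the document does not give, and no loss due to the percentage scale itself is shown. The point still needs correcting before unblinding, because it concerns which variable decides the trial.

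**What to change.** Define one primary variable per scale, in points: the MoCA score, and likewise the MES score, at week 8, compared between arms with adjustment for the week-0 score. This estimates the same treatment effect as baseline-adjusted change, so the wording about change in the abstract and Study design can be kept in that form. Name week 0 explicitly, because Table 1 schedules both scales at week −1 and at week 0 and the formula does not say which is the pretreatment score. Keep the margins in points. Make the improvement rate a supportive summary. Align the abstract, Study design, Primary outcomes and Sample size calculation before the first unblinding, which the Blinding method section places after the data file is locked.

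The cost is wording only. Table 1 already schedules both scales at weeks 0 and 8, so no new data are needed. The sample size need not rise on this account: the unadjusted SD of 2.21 is conservative for the adjusted analysis if post-treatment scores correlate with baseline. The registry entry is not among the documents, so whether it also needs changing cannot be said here.

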#### Secondary outcomes

Secondary outcome measures are the FAQ and TCM symptom scale scores before and after intervention. The change in activities of daily living is closely related to the change in cognition and could sensitively reflect the changes in patients' conditions. The FAQ scale involves complex social functions and daily activities and is suitable for the evaluation of patients with mild symptoms. According to the *Guidance Principle of Clinical Study on New Drug of TCM* (2002) [18], we score the change in TCM syndromes of participants before and after intervention.

We will use cognitive event-related potentials (ERPs) as the objective indicator for the assessment of cognitive status. ERP measurement is a sensitive method for detecting cognitive decline, inducing prolonged latency of P300 waves, and has certain specificity for the diagnosis of MCI. Serum homocysteine (HCY) will be detected pre- and posttreatment. Many prospective studies have found that increased t-HCY remained associated with cognitive impairment, which has significant implications for public health [19, 20].

#### Safety evaluation

For the safety evaluation, routine blood, liver function (alanine aminotransferase (ALT) and aspartate aminotransferase (AST)), renal function (blood urea nitrogen (BUN) and creatinine (Cr)), urine, and faecal tests and electrocardiograms will be performed before treatment and after 8 weeks of intervention. Vital signs and all adverse events will be recorded at every study visit during the trial. In case of any adverse event during the study, the clinician in charge of the case shall carefully record the details, including the name and characteristics of the adverse event, occurrence and disappearance time, treatment measures, impact on the primary disease and prognosis, in the CRF.

#### Data management and monitoring

Shanghai Municipal Hospital of Traditional Chinese Medicine will assign an independent quality inspector to oversee the process of the clinical trial. Furthermore, we will strengthen the exchange by telephone or other communication means. The purpose of supervision is as follows: (1) to ensure compliance with the protocol; (2) to ensure the completeness and accuracy of the information entered into the CRF and the dispensed study drug return records; (3) to protect the rights of participants; and (4) to check the accuracy, completeness and legality of the data.

### Statistical plan

#### Sample size calculation

The necessary sample sizes were calculated for the two primary outcomes, namely, the MoCA and MES. With reference to our previous study [21], the following parameters were used: the mean MoCA score (*μ*_r_) in the treatment group was 25.67; the mean MoCA score (*μ*_c_) in the control group was 23.36; we assumed that the superiority margin (Δ) was 1.20; the standard deviation (σ) was 2.21; the type I error rate (α) was set to the usual level, a unilateral value of 0.025), with Z_α/2_ = 1.96, the type II error rate (β) was set to a unilateral value of 0.05, with Z_β_ = 1.645; the ratio (K) of the treatment group size (*n*_1_) to the control group size (*n*_2_) was K = 1 (*n*_1_ = *n*_2_ = 104). Considering that there are three research centres in this study and a 20% dropout rate, the logistic regression analysis suggested that the sample size should be 15 to 30 times the number of indices being analysed plus an extra 30 patients, for a total required sample size of 280 patients (140 patients per group).

For the second primary outcome, we set the mean MES scores to 82.83 in the treatment group and 73.50 in the control group, with an SD of 7.83 [22]. We assumed that the superiority margin was 3.92 (1/2 standard deviation); we calculated that we would need a total of 122 patients (66 per group) to allow for a 20% dropout rate. Of the necessary sample sizes estimated for the two primary outcomes, the larger value was selected as the sample size for this study. The formula for calculating the sample size is as follows:

$$\begin{array}{c}{\mathrm n}_{\mathrm c}=\frac{\left({\mathrm Z}_{\displaystyle\mathrm\alpha/2}\;+\;{\mathrm Z}_{\mathrm\beta}\right)^2\;\mathrm\sigma^2\;\left(1+{\displaystyle\frac1{\mathrm k}}\right)}{\left(\mu_r-\mu_c-\mathit\triangle\right)^2}\\{\mathrm n}_{\mathrm r}={\mathrm{Kn}}_{\mathrm c}\end{array}$$

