### Statistical analyses

In this study, the data analysis will be performed on the full analysis set (FAS), per protocol set (PPS) and safety analysis set (SS). The efficacy analysis will be conducted on an intention-to-treat (ITT) basis. The 95% confidence intervals (CIs) will be calculated as exact CIs. For the two primary outcomes, the *P*-value will be adjusted to 0.033. This value was based on a recommendation to divide the pre-specified *P*-value threshold by the value halfway between 1 (representing no adjustment) and the number of primary outcome comparisons (the denominator used for the Bonferroni correction) [23]. All statistical tests are 2-sided, and unless otherwise stated, *P* < 0.05 will be considered statistically significant. When the primary outcome measures are missing, the researchers will combine statistical analysis and clinical experience to judge whether to exclude the subject or replace the missing data with the last observation carried forward (LOCF).

The measurement data will be subject to normal distribution and homogeneity of variance, which is expressed as the mean ± standard deviation. Comparisons between groups will be performed using an independent 2-sample t test. Comparisons between multiple time points will be analysed using repeated-measures ANOVA, multivariate ANOVA or paired t test. When the data do not meet the criteria of normality and homogeneity, the results will be expressed as the median. The Wilcoxon rank sum test will be used to compare differences between groups. Before and after treatment, numerical variables and ordered categorical variables measured over multiple time points will be analysed using generalized estimating equations and a mixed effects model. The enumeration data will be expressed as frequency (n), constituent ratio (%) or ratio (%). If the variable data type is unordered, categorical comparisons between groups will be performed by the χ^2^ test. The ordered categorical variable data will be analysed using the rank sum test. Comparisons of two-way ordered data with different properties within contingency tables will be made with the linear chi-square test or rank sum test. Multivariate data analysis will be conducted using multiple linear regression, the K-M test, Cox regression or a trend test. All statistical analyses will be performed with IBM SPSS Statistics 24.0.

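### Sample size: the MoCA figure of 104 per group reproduces, but the MES total and its dropout allowance are wrong, both outcomes are sized at a looser alpha than is tested, and 280 cannot be traced

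*Protocol article*

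**What the plan says.** All of the sizing is in the protocol article under Sample size calculation.

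- **MoCA.** The mean "in the treatment group was 25.67" and "in the control group was 23.36", "the superiority margin (Δ) was 1.20" and "the standard deviation (σ) was 2.21". Alpha "was set to the usual level, a unilateral value of 0.025" (Z = 1.96), beta is 0.05 (Z = 1.645) and allocation is 1:1. The result is 104 per group.
- **MES.** Means of 82.83 and 73.50, SD 7.83 and margin 3.92. The result: "we calculated that we would need a total of 122 patients (66 per group) to allow for a 20% dropout rate".
- **Total.** The step to 280 (140 per group) cites three centres, 20% dropout, a rule under which "the logistic regression analysis suggested that the sample size should be 15 to 30 times the number of indices being analysed", and 30 further patients. The section then says that the larger of the two outcome-based sizes was taken.

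Under Statistical analyses, for the two primary outcomes the P-"value will be adjusted to 0.033", and all tests are two-sided. The multivariable methods named there are multiple linear regression, Kaplan-Meier, Cox regression and a trend test.

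**The concern.** The article prints its inputs, its formula and its results, so a reader can check them. Three things fail the check.

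- The MES sentence contradicts itself, and neither of its two figures is what a 20% loss requires.
- The alpha in the sizing is not the alpha in the analysis, so the stated 95% power does not apply to the tests that will be run.
- The final total is explained by a rule with a missing input, for a type of model that the analysis section does not name.

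At stake is whether the stated power can be relied on and whether 280 has a basis that a reader can follow.

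**Working it through.** **Formula (from the article, k = 1):** n per group = (Zα/2 + Zβ)² × σ² × 2 / (difference − margin)².

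**1. MoCA at the stated alpha.** Net difference = 25.67 − 23.36 − 1.20 = 1.11. (1.96 + 1.645)² = 12.996. n = 12.996 × 4.8841 × 2 / 1.2321 = 103.03, rounded up to 104. The printed figure reproduces.

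**2. MES at the stated alpha.** Net difference = 82.83 − 73.50 − 3.92 = 5.41. n = 12.996 × 61.3089 × 2 / 29.2681 = 54.45, rounded up to 55 evaluable per group.

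**3. MES dropout.**
- 55 × 1.2 = 66, which is the printed per-group figure.
- Losing 20% of 66 leaves 52.8, about 53, which is below 55. Power at 53 is about 94.5%.
- The number to enrol is 55/0.8 = 68.75, rounded up to 69 per group, 138 in total.
- 2 × 66 = 132, not 122. Read as a total, 122 is 61 per group. After 20% loss about 49 remain, with power about 92.8%.

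**4. The tested alpha.** Two-sided 0.033 has Z = 2.132, and (2.132 + 1.645)² = 14.266.
- MoCA: 14.266 × 4.8841 × 2 / 1.2321 = 113.1, rounded up to 114 evaluable; 114/0.8 = 142.5, so 143 per group and 286 in total.
- MES: 14.266 × 61.3089 × 2 / 29.2681 = 59.8, rounded up to 60 evaluable; 60/0.8 = 75 per group and 150 in total.
- MoCA power with 104 evaluable: SE = 2.21 × √(2/104) = 0.3065; Φ(1.11/0.3065 − 2.132) = Φ(1.490) = 93.2%.

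**5. What 280 gives.** 140 × 0.8 = 112 evaluable per group.
- MoCA at 0.033: SE = 2.21 × √(2/112) = 0.2953; Φ(1.11/0.2953 − 2.132) = Φ(1.627) = 94.8%. At two-sided 0.05 it is 96.4%.
- MES at 0.033: SE = 7.83 × √(2/112) = 1.0463; Φ(5.41/1.0463 − 2.132) = Φ(3.04), above 99.8%.

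**6. Can 280 be derived?** Under the rule, (280 − 30)/15 = 16.7 and (280 − 30)/30 = 8.3. Any whole number of indices from 9 to 16 therefore fits some multiplier in the range. Without that number the rule does not fix 280 and cannot be checked.

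**The case against.** The strongest reply is that nothing in the trial changes. The outcome that sets the size is MoCA, and its figure is correct. MES needs at most 150 of the 280 patients. A trial of 122 will not be run, so its shortfall in power is hypothetical. All of this stands, and it is why the point is minor.

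A second reply is that 280 may have a simple origin: 208 × 1.2 + 30 = 279.6, using the printed 20% and the printed 30. That is plausible, but the article does not show it. It would also repeat the inflation by 1.2 and leave the 30 unexplained.

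A third is that the analysis section describes a two-sided t test and no test against a margin. For the plain MoCA difference of 2.31, the formula at 0.033 needs 14.266 × 4.8841 × 2 / 5.3361 = 26.1, so 27 per group, and the change of alpha would then have no practical effect. This stands as a limit: every power figure given here applies to the article's formula with its superiority margins.

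A reader might also infer that logistic regression has no place anywhere in the plan. The article is a condensed account and does not support that. It shows only that its analysis section names no logistic regression and that its sizing section gives no number of indices.

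**Conclusion.** The point holds as a minor error in the stated figures. The MES total contradicts its per-group number by 10 patients, and the per-group number is 3 short of what 20% loss requires. The sizing alpha is looser than the tested alpha, which lowers MoCA power at 104 evaluable per group from 95% to 93.2%. The basis for 280 cannot be followed from what is printed.

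Two stronger readings are tempting, and the document does not support either. The first is that the sample-size statement as a whole does not reproduce; the MoCA figure, which governs, reproduces exactly. The second is that the trial is underpowered; on the stated assumptions 280 falls short of 95% for MoCA by about 0.2 percentage points, or 6 patients against 286, and is ample for MES.

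These results rest on the article's means, SDs and margins, its normal-approximation formula, 20% loss in each group, and 0.033 taken as printed. With 0.05/1.5 = 0.0333 unrounded, MoCA needs 113 evaluable per group instead of 114.

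**What to change.** Correct the text; enrolment stays at 280.

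- **Size both outcomes at two-sided 0.033 and divide by 0.8 for dropout.** MES: 60 evaluable, 75 per group, 150 in total (at 0.05: 55, 69 and 138). MoCA: 114 evaluable, 143 per group, 286 in total.
- **Keep the 20% dropout and the total of 280.** State that 112 evaluable per group gives about 94.8% power for MoCA and above 99.8% for MES at 0.033, under the article's formula with its superiority margins.
- **Replace the logistic-regression rule** as the basis for 280 with that power statement, or name the model and its number of indices. Do not simply delete the sentence, because it also carries the MoCA dropout rate and the total.

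The cost is a few sentences. No patients, visits or analyses change.
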